##### Measures

All effectiveness and implementation outcome data collected in Phase 2 will be fully deidentified data extracted from the medical record. Counselor data will only be extracted for those who completed the MBC workshop, whereas patient data will only be extracted for those treated by counselors who completed the workshop. Patient treatment engagement data and opioid abstinence will be collected monthly across 6 months prior to and post MBC integration to evaluate preliminary effectiveness and implementation. Counselor MBC exposure and fidelity will be assessed post MBC integration only. Demographic data will also be extracted for all counselors and patients (e.g. age, biological sex, race, ethnicity). Finally, information about prior treatment at the OTP (i.e. patients who received care previously but came in again as new patients), patient MOUD type and dose, and patient DSM diagnoses (including other substance use or mental health disorders) will be extracted.

Patient treatment engagement: The primary MBC effectiveness outcome measure is patient treatment engagement, which we have broadly defined to encompass both completion of methadone/buprenorphine dosing visits and attendance at counseling/psychosocial intervention appointments. Approximately 20 charts per site (*N* = 80) will be randomly selected from new patients that entered treatment over the 6 months prior to MBC integration. An additional separate set of 20 new patient charts per site (*N* = 80) will be extracted to evaluate treatment engagement in the 6 months following integration. Charts will be reviewed to identify the proportion of treatment visits attended (i.e. MOUD dosing visits and individual/group counseling appointments) out of total visits scheduled for each patient, as well as the total number of weeks each patient was retained in treatment.

Patient opioid abstinence: The secondary MBC effectiveness outcome measure is patient opioid abstinence. The same charts extracted for treatment engagement will also be reviewed for opioid abstinence. Charts will be reviewed to identify the proportion of negative opioid urine screens for each patient monthly across 6 months prior to and post MBC integration. We anticipate that some patients in our chart sample will discontinue treatment (e.g. due to discharge or leaving the OTP) during the 6 months prior to and post MBC integration. For patients who discontinue treatment, opioid abstinence will be calculated as the proportion of negative urine screens for each month that they were present in the program. We will include an indicator in the data set to denote that urine drug screen data was unavailable for the months following patient treatment discontinuation.

Counselor MBC exposure: The primary MBC implementation outcome measure is monthly counselor MBC exposure. Counselor-level exposure refers to the number of group counseling sessions each month where MBC was administered divided by the total number of group sessions completed each month by OTP counselors (i.e. total opportunities to use MBC) [62]. The total number and dates of monthly completed group counseling sessions delivered by counselors who attended the MBC workshop. will be extracted from the EMR at all four sites. Documentation from each of these counseling sessions will be reviewed to determine whether or not MBC was recorded. Monthly MBC exposure values will be computed by dividing the total number of sessions with MBC documentation by the total number of sessions completed across each of the 6 months post MBC integration.

Counselor MBC fidelity: The secondary MBC implementation outcome measure is monthly counselor MBC fidelity. Counselor MBC fidelity refers to the degree to which counselors use MBC according to the established protocol (i.e. administering the questions, reviewing responses, discussing responses with patients in group counseling). Fidelity data will be computed as a categorical variable for completed group counseling sessions delivered by counselors who attended the MBC workshop across 6 months post integration. Counselors will receive a “1” if they documented MBC administration, a “2” if they documented administration and response review or administration and MBC discussion, and a “3” if they documented administration, response review, and MBC discussion with the patient. All attended counseling sessions without MBC documentation will receive a “0” [19].

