##### Participant selection

Leaders and counselors will be actively recruited, and patient records will be extracted from the electronic medical record. The Phase 1 eligibility criteria will be used to determine eligibility of counselors and leaders (see Phase 1. Participants). Patient records will be included in data extractions if the patients were receiving methadone or buprenorphine along with group counseling; and were inducted on medication for opioid use disorder within 6 months of MBC integration. We anticipate that the demographics of the Phase 2 participants will be similar to those in Phase 1.

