##### MBC delivery

The MBC protocol will be adapted based on RAPICE results. Anticipated MBC core delivery steps are presented in Fig. 2. The process, which aligns with MBC as delivered in group substance use treatment in the Veteran’s Administration [22, 36–38], will begin with the counselor administering MBC questions at the start of each group session via paper/pencil response forms. The counselor will then review each patient’s responses confidentially and use the responses to guide the agenda for the group session. For example, counselors may use responses to prompt group discussion about symptoms present for multiple group members, shift the session focus to target patient needs, discuss specific responses with individual group members during or following the group session, or use MBC responses to flag patients for follow up individual counseling or case management (i.e. treatment plan changes). Counselors may also use information regarding trends in group members’ MBC responses over time to highlight areas of improvement during the group session and plan group content for future sessions (e.g. focusing on specific skills or topics). Following each group session, counselors will document MBC delivery and responses in the health record to enable monitoring of change over time, in accordance with the MBC integration plan described below.

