##### MBC integration

Informed by existing OTP workflow and health record documentation data gathered via RAPICE, researchers will meet with relevant leaders and information technology specialists at each of the OTPs to integrate the adapted MBC protocol into the workflow. Similar to Phase 1, each OTP will sign an Organization Participation Agreement outlining Phase 2 activities that will include an agreement to make electronic medical record changes to integrate MBC and extract de-identified data. At the beginning of the integration process, researchers will complete a second round of clinic site visits focused on integration of MBC into both group counseling and documentation procedures using collaborative research design principles [59–61]. The collaborative design approach will include meetings with leaders, counselors, and associated information technology specialists at each site to evaluate MBC documentation needs. OTPs provide a wide range of group counseling services covering numerous topics (e.g. recovery support, Cognitive Behavioral Therapy), and we anticipate that some patients may attend multiple groups each week. As a result, collaborative meetings will also focus on identifying which groups would be most appropriate for MBC integration. Informed consent will be obtained from all leaders and counselors participating in integration meetings. Up to 40 (approximately 8 to 10 per site) participants will be invited to contribute to meetings, each of which will be will be compensated $50.

The multi-site OTP organizations participating in this study use electronic medical record systems that can be modified by adding new templates, checklists, and/or dot phrases to facilitate documentation. Investigators will meet with appropriate health data specialists to determine an MBC documentation plan, which will be followed by changes to the electronic medical record interface based on feasibility and counselor needs. These electronic medical record changes may vary from a full, automated integration of MBC into provider documentation to the addition of simple dot phrases or note templates. Meetings with health data specialists will also involve development of methods for the OTPs to extract fully deidentified MBC outcome data from the electronic medical record [59, 61].

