##### Sample size and power considerations

For Phase 2, previous studies of MBC have demonstrated small to large treatment effect sizes (Hedges’ *g* ranges from 0.10 to 0.53; Cohen’s *d* ranges from 0.18 to 0.50) [63]. A small to medium effect size in this study for either treatment engagement or opioid abstinence, paired with evidence of counselor acceptability and feasibility from the Phase 1 RAPICE, would indicate preliminary support for a larger trial of MBC in opioid treatment programs. The Phase 2 sample size of 160 (*N* = 80 new patient charts pre-MBC EMR integration and 80 charts post-EMR integration) is powered to detect a small to medium effect size of 0.39 using a basic pre- to post-test design. The detected MBC effect size in this study will be used to calculate post-hoc power analyses to determine the number of patients required for a fully-powered, two-group (MBC versus services as usual) effectiveness-implementation trial. For example, a sample size of 484 patients would be required to detect small effect sizes (*d* = 0.3), while a smaller sample of 176 patients would be required to detect medium effect sizes (*d* = 0.5). For large effect sizes, a sample of 70 patients would be required (*d* = 0.8).

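### Chart eligibility is not tied to the groups chosen for MBC, so the post-MBC sample can include patients for whom no MBC session is planned

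*Protocol article*

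**What the plan says.** Three parts of the Phase 2 text bear on this.

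**Who is sampled.** Participant selection (Phase 2) states: "Patient records will be included in data extractions if the patients were receiving methadone or buprenorphine along with group counseling", together with a recent-induction condition. Measures adds that "patient data will only be extracted for those treated by counselors who completed the workshop". Neither names a type of group. About 20 new-patient charts per site are taken in each period (80 pre, 80 post, different patients), and the data analysis section compares the pre and post means by t-test with no restriction by group.

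**Where MBC goes.** MBC integration notes that programs run many kinds of groups and adds: "we anticipate that some patients may attend multiple groups each week". It concludes that "collaborative meetings will also focus on identifying which groups would be most appropriate for MBC integration". How many groups, or what share, is left open.

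**How delivery is described and counted.** MBC delivery, setting out anticipated steps, says the process "will begin with the counselor administering MBC questions at the start of each group session via paper/pencil response forms". In Measures, the denominator of counselor exposure is the "total number of group sessions completed each month by OTP counselors (i.e. total opportunities to use MBC"). Fidelity is scored over completed group sessions of trained counselors, and a session with no MBC documentation scores 0. No exception is made for groups not chosen for MBC.

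**The concern.** The chart rule and the delivery plan use different units. The rule works by counselor, while the placement of MBC works by group. If a trained counselor runs one group with MBC and one without, patients of both groups enter the post sample on equal terms, although MBC is planned only for the first. Such patients pull the pre-post difference toward zero.

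This matters because Sample size and power considerations treats a small-to-medium effect on engagement or abstinence, together with Phase 1 acceptability evidence, as preliminary support for a larger trial. It then uses the detected effect to size that trial. An attenuated estimate weakens the first use and inflates the second.

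The implementation measures have a related problem. If some of a counselor's groups are not designated, their sessions count as missed opportunities for exposure and score 0 for fidelity. Both measures would then mix how MBC was placed with what counselors did, and that mixture would carry into the exploratory model linking fidelity to patient outcomes.

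**Working it through.** **1. The protocol's own figure.** "The Phase 2 sample size of 160" (80 pre, 80 post) is said to detect an effect of 0.39. Alpha, sidedness and power are not stated, so they are assumed here. For two independent groups of 80, detectable d = (z_alpha + z_power) × √(2/80).
- One-sided 0.05, 80% power: (1.645 + 0.842) × 0.158 = 0.393 (0.395 with the t distribution). This matches 0.39. Power at exactly 0.39 is 79%.
- Two-sided 0.05, 80% power: 0.446. This does not match, and power at 0.39 is then 69%.
- The future-trial totals in the same section (484, 176 and 70 for d = 0.3, 0.5 and 0.8) reproduce exactly at one-sided 0.05 with 95% power. This supports a one-sided convention but does not prove it.

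**2. Dilution model.** Let q be the share of post charts from patients scheduled only into groups without MBC. Assume no effect on those patients, no spillover from a trained counselor's other groups, the same mix of patients across groups in both periods, and an unchanged SD. Then:

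observed d = (1 - q) × true d

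The unchanged-SD assumption does little harm. The mixture adds q(1 - q)d² to the post variance, at most 0.25 × 0.39² = 0.038 on a variance of 1.

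**3. Results for true d = 0.39 and 80 v 80 charts.** The values of q are assumed, because the document gives none.

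| q | observed d | power, one-sided 0.05 | power, two-sided 0.05 | total charts for 80% power, one-sided |
|---|---|---|---|---|
| 0 | 0.390 | 79% | 69% | 164 |
| 10% | 0.351 | 71% | 60% | 204 |
| 20% | 0.312 | 63% | 50% | 256 |
| 30% | 0.273 | 53% | 40% | 334 |
| 50% | 0.195 | 34% | 23% | 652 |

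**4. Effect on sizing the next trial.** On the protocol's own figures, a true d of 0.5 with q = 40% would appear as 0.6 × 0.5 = 0.3. The calculated future trial would move from 176 to 484 patients.

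**5. Exposure ratio.** If a share p of a counselor's group sessions belongs to designated groups and MBC is given in every one of them, exposure is still p. With p = 0.5 (again assumed), perfect delivery would be recorded as 50%.

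**The case against.** The strongest reply is that the document never says any group will be left out. It says only that meetings will identify suitable groups, and gives overlapping attendance as one reason. A patient in several groups may well meet MBC in one of them. MBC delivery speaks of each group session, and the exposure and fidelity definitions treat every session of a trained counselor as an opportunity. On that reading the chart rule is consistent with the measures, and q is zero. The trained-counselor filter also removes some unexposed patients already. All of this stands. A reader might infer that the post sample is bound to include patients who can never receive MBC; the document does not support that. It supports only that the stated rule would admit them if a site chose some groups and not others.

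A second reply is that hypotheses 1 and 2 concern change across sites after integration, so a wider sample answers a legitimate program-level question, and the same rule applies in both periods. This stands in part. The wider target would be defensible if stated. But the sample is not program-wide as written, because patients of untrained counselors are excluded. The filter moves toward patients with access to MBC and stops short of the group.

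A third reply is that group placement and extraction methods are to be worked out with the sites, and that a fuller protocol exists. A list of group codes can indeed wait. The inclusion rule, however, is already fixed in the article, and it does not allow for the group selection the article also plans.

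**Conclusion.** The point holds as a mismatch between the chart rule and the planned placement of MBC, with attenuation as a possible consequence. If a share q of post charts comes from patients scheduled only into groups without MBC, an effect of 0.39 appears as about 0.35, 0.31 or 0.20 at q = 10%, 20% or 50%. One-sided power falls from 79% to 71%, 63% or 34%. These figures rest on assumed q, one-sided alpha of 0.05, no spillover and a stable patient mix.

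The document does not show that the dilution will be large, or that it will occur at all. Nor does it set a pass/fail threshold that a diluted estimate would miss: the small-to-medium effect is described as preliminary support, alongside acceptability evidence. The descriptions of delivery at each session, selection of groups, the exposure denominator and the zero fidelity score do need to be reconciled. The amendment is worth making because it is cheap and can precede any Phase 2 data.

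**What to change.** In Phase 2 Participant selection and in Measures, add a rule for any site that designates only some groups for MBC:
- Post charts are drawn from new patients scheduled into a designated group.
- Pre charts are drawn from new patients scheduled into the same groups, or the same group types at that site, in the pre window.
- Selection rests on scheduling in both periods. It should not rest on recorded receipt of MBC, since filtering the post charts by receipt would add selection bias.

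If the wider target (all group patients of trained counselors) is the one intended, state that instead and note that the estimate averages over patients without planned MBC.

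Also reconcile MBC delivery, MBC integration and the exposure and fidelity definitions, so that sessions of non-designated groups are neither counted as opportunities nor scored 0.

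The cost is one more filter (group name or code) in the extraction. The sampling frame per site becomes smaller, and a group created for MBC needs a matched pre-period group type. Phase 2 is not yet registered and Phase 1 data collection is only beginning, so the change can be made in time.

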The Measurement-Based Care to Opioid Treatment Programs (MBC2OTP) Project addresses the need to advance the uptake of MBC in OTPs via three specific aims. Aim 1 is to inform MBC implementation via a novel mixed methods approach, Rapid Assessment Procedure Informed Clinical Ethnography (RAPICE) [42]. RAPICE embeds participant observation within front-line study team members and treatment providers engaged in rolling-out clinical procedures, combined with regular data review/analyses with an implementation science mixed methods expert consultant [42]. Aim 2 is to apply the RAPICE mixed-methods results to adapt an MBC assessment protocol for OTP use. Aim 3 is to simultaneously evaluate both effectiveness and implementation outcomes via a hybrid type 1 effectiveness-implementation trial. No a priori hypotheses were developed for Aims 1 and 2 given their exploratory nature and focus on development of an MBC protocol. Aim 3 will test the following hypotheses: (1)* Treatment engagement will increase across all sites following MBC electronic medical record integration*; (2) *Negative opioid urine screens will increase across all sites following MBC electronic medical record integration*; (3)* The extent to which counselors deliver MBC with fidelity will be positively associated with patient engagement in treatment sessions (both medication dosing and counseling appointments) and patient opioid abstinence across all sites.*

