## Methods

### Study overview

The MBC2OTP Project has two phases. Phase 1 involves RAPICE methodology with eight OTPs, which combines rapid assessment procedures with clinical ethnography to facilitate partnership building and enhance the efficiency of data collection [42]. Phase 2 will consist of a pilot hybrid type 1 effectiveness-implementation trial in which the four OTPs selected during Phase 1 will engage in a collaborative design approach to integrate the refined MBC protocol into their workflow. This study is reported in line with SPIRIT guidelines (see SPIRIT Checklist in Additional file 1). Table 1 depicts a full study timeline.

**Table 1 Tab1:** Phase 1 and 2 study timelines and associated activities

	Study period																			
	Year 1				Year 2				Year 3				Year 4				Year 5			
Phase 1/aims 1 and 2: RAPICE																				
Project launch	X	X	X																	
RAPICE stage 1: clinic site visits		X	X	X	X															
RAPICE stage 1: qualitative interviews			X	X	X															
RAPICE stage 1: quantitative surveys			X	X	X															
RAPICE stage 2: mixed methods data analysis					X	X	X													
RAPICE stage 3: MBC site selection							X	X												
RAPICE stage 3: MBC protocol adaptation								X	X											
Phase 2/aim 3: pilot MBC implementation																				
MBC EMR integration meetings												X	X							
MBC EMR integration site visits													X	X						
MBC workshop training and ongoing support															X	X				
MBC EMR patient outcome data extraction										X	X						X	X		
MBC EMR implementation outcome data extraction																	X	X		
MBC data analysis																		X	X	X

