Once MBC has been integrated into the electronic medical record, OTP counselors will be invited to complete a 4-h MBC training workshop led by the investigative team. In addition, ongoing support (e.g. supervision) will be offered to counselors based on Phase 1 RAPICE feedback. Shortly after the workshop, counselors will begin using MBC and documenting all three steps (i.e., administration, review of responses, discussion with patients) in the electronic medical record.

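### The pre and post windows count from EMR integration although MBC starts only after a later workshop, and pre charts are scheduled before the workshop-counselor restriction can be applied

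*Protocol article*

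**What the plan says.** **Time zero.** The first Aim 3 hypothesis, at the end of the introduction, reads "Treatment engagement will increase across all sites following MBC electronic medical record integration". The Measures section says "Patient treatment engagement data and opioid abstinence will be collected monthly across 6 months prior to and post MBC integration" and draws the pre charts from "new patients that entered treatment over the 6 months prior to MBC integration". Phase 2 Participant selection ties chart eligibility to induction within 6 months of integration. Measures also counts exposure and fidelity over the 6 months after integration. Sample size and power considerations labels its two sets of 80 charts as before and after EMR integration.

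**Order of events.** The MBC integration section says "Once MBC has been integrated into the electronic medical record, OTP counselors will be invited to complete a 4-h MBC training workshop", and then "Shortly after the workshop, counselors will begin using MBC and documenting all three steps".

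**Restriction.** Measures states that "patient data will only be extracted for those treated by counselors who completed the workshop". It makes no distinction between pre and post charts.

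**Schedule.** Table 1 has separate rows for "MBC EMR patient outcome data extraction", for integration meetings and site visits, and for "MBC workshop training and ongoing support". The Methods part of the Abstract places the chart reviews themselves in the 6 months on either side of integration.

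**The concern.** Two things do not fit together.

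1. The clock for the post window starts at a step that precedes the intervention. Time between EMR integration and first MBC use would count as post-MBC although no MBC is delivered. The effectiveness estimate would shrink. Exposure, the primary implementation outcome, would include sessions in which MBC could not yet have been used. Fidelity would be 0 for those sessions, because every attended session without MBC documentation scores 0. The sample-size section uses the observed effect to size the next trial, so a diluted estimate would carry forward.

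2. The pre charts are limited to patients of counselors who completed a workshop, but are scheduled for extraction before any workshop. If the restriction were then applied only to the post charts, the comparison would set patients of counselors who took up training against patients of all counselors. That difference could not be separated from the effect of MBC.

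**Working it through.** **Reading Table 1.** Each row has 20 cells under five years, so four per year. The text supports reading them as quarters: Phase 1 is about 27 months (27/3 = 9 quarters) and Phase 2 about 33 months (33/3 = 11 quarters), and 9 + 11 = 20. The last Phase 1 activity is in column 9 and the first Phase 2 activity in column 10.

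| Row | Columns | Quarters |
|---|---|---|
| Patient outcome extraction, first block | 10–11 | Y3Q2–Q3 |
| Integration meetings | 12–13 | Y3Q4–Y4Q1 |
| Integration site visits | 13–14 | Y4Q1–Q2 |
| Workshop and support | 15–16 | Y4Q3–Q4 |
| Patient outcome extraction, second block | 17–18 | Y5Q1–Q2 |

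**Intervals.** Columns 12, 13 and 14 lie between the first extraction block and the workshop row: 3 quarters, about 9 months. Columns 12 to 16 lie between the two extraction blocks: 5 quarters, about 15 months.

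**Testing each possible date for integration.**

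- *Start of integration work (start of Y3Q4).* The 6 months before are Y3Q2–Q3, which matches the first block. The 6 months after are Y3Q4–Y4Q1, which end before the workshop row begins in Y4Q3.
- *Completed EMR integration (end of Y4Q2).* The 6 months before are Y4Q1–Q2, which an extraction in Y3Q2–Q3 cannot cover. The 6 months after are Y4Q3–Q4, the quarters of the workshop and support row.
- *First MBC use (Y4Q3 at the earliest).* The 6 months before start no earlier than Y4Q1, again after the first block has ended. The second block can fit.

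No single date satisfies both blocks and the stated order of events.

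**Untreated share of the post window.** With a lag of L months from EMR integration to first MBC use, the share of a 6-month window without MBC is L/6. The documents do not give L. For assumed values of 0, 1, 2 and 3 months the share is 0, 17%, 33% and 50%. These show how the result scales; they are not estimates. If the effect accrued only in exposed months and in proportion to them (a further assumption), the estimate would be multiplied by 1 − L/6. A counselor who used MBC in every session from first use would still show zero exposure and fidelity 0 in each whole month before it.

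**Restriction.** During Y3Q2–Q3 no counselor has attended a workshop, so the list that defines eligible pre charts does not exist at the scheduled extraction.

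**The case against.** The best defence reads integration as a process. The section headed MBC integration covers the meetings, the EMR changes, the workshop and the support. Measures and Phase 2 Participant selection speak of MBC integration, without the EMR qualifier. If integration runs from Y3Q4 to Y4Q4, the 6 months before it are Y3Q2–Q3 and the 6 months after it are Y5Q1–Q2, and both Table 1 blocks fit. This reading is coherent and may be what was meant. It does not agree with the hypotheses or the sample-size text, which name EMR integration, or with the sentence that places the workshop after EMR integration. It also leaves the restriction on pre charts unresolved.

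Other parts of the defence stand:

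- A reader might infer that the pre charts are taken long before both integration and the workshop. Table 1 supports this for the workshop and for completed integration only; the first block directly adjoins the first integration meetings.
- A reader might infer that the counselor restriction can never be applied to pre charts. Charts remain in the EMR, so they can be pulled, or filtered by a counselor code, after the workshops. The conflict is with the schedule as written.
- A reader might turn the lag into a loss of power. Nothing in the documents supports a value: the workshop lasts 4 hours, use follows soon after it, and the Y4Q3–Q4 row includes ongoing support as well as training.
- A reader might charge Table 1 with a stated multiple of secular drift. That requires reading the blocks as data windows. Exposure to secular change also belongs to the pre–post design, and the Discussion already acknowledges the lack of a concurrent comparison.

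A condensed article can leave exact site dates to the full protocol. Here, however, the statements that are printed conflict with each other.

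**Conclusion.** The concern holds in two limited parts.

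First, the windows, exposure and fidelity are counted from integration, specified as EMR integration in the hypotheses and sample-size text, while MBC begins only after a later workshop. Followed literally, the post window can include time without MBC. The direction is clear: a diluted effect, lower exposure, and fidelity scores of 0 before MBC is in use. The size is not known, because it depends on an unstated lag; each month of lag is one sixth of the window.

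Second, the first chart extraction ends three quarters before the workshop row begins, so the restriction to patients of workshop completers cannot be applied at that extraction. This rests on reading Table 1 cells as quarters, which the stated phase lengths support, and on the rows marking when charts are pulled, as the Abstract suggests. Restricting the post charts alone would confound the primary effectiveness comparison.

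The documents do not support a specific loss of power, a multiple of secular drift, or a claim that the restriction is unworkable in principle. The point should be settled before Phase 2 begins. It affects the primary comparison and both implementation outcomes, and it is cheap to correct while Phase 1 data collection is only starting.

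**What to change.** 1. Start each site's 6-month post window, for patient outcomes, exposure and fidelity alike, at first MBC use after that site's workshop.
2. End each site's 6-month pre window at a stated site date before MBC use. Treat the integration and training interval as a washout that belongs to neither window.
3. Pull both chart sets retrospectively after the post window closes, and apply the same list of workshop counselors to both.
4. Align the Abstract, the Aim 3 hypotheses, Phase 2 Participant selection, Measures, Sample size and power considerations, and Table 1 with these dates.

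**Cost.** A text and table edit, and one extraction in place of two, with no early look at the pre data. If a site first uses MBC at the end of Y4Q4, its post window closes at the end of Y5Q2. The pull would then fall after the extraction quarters now in Table 1, and the analysis, now starting in Y5Q2, would begin later.

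**Downsides to state.** The washout leaves a calendar gap between the windows that is open to secular change. If the pre window ends when integration work starts, it is the same Y3Q2–Q3 block as now, so the gap is not shortened. The common counselor list also limits the pre charts to counselors who stayed long enough to attend; the protocol expects to recruit about 20% additional staff because of turnover.
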